#### **7.5.4 Difference between intervention and comparator**

In both HDF and HD, toxins are removed by diffusion. The difference between the two treatments is that HDF also involves (i) convection to remove 23+L of toxin-containing fluid and (ii) substitution/ replacement of that volume with 21+L of fluid. As this fluid is being given directly into the patient's blood stream, it needs to be of a high degree of purity than is required for high-flux HD – sterile rather than ultra-pure (see Box 1).

For the patient, the treatments will appear very similar. The fluid removal and substitution/replacement occurs "within" the dialysis machine. Patients in both arms will need to come in to their dialysis unit for treatment three times a week for ~4 hours each time. Access to the blood for most patients is likely to be an AV fistula or graft so that sufficient blood flows can be achieved (i.e. not a plastic neck line, which is used in ~15% of patients). These AV fistulae and grafts will be needled in the same way for both groups for the blood to circulate out through the dialysis machine, though the needle gauge and blood pump speeds may need to be increased slightly in the HDF group to achieve the necessary convection volume.

### **7.6 Long term follow-up assessments**

Follow up will continue for a minimum of 32 months and a maximum of 91 months. It will be undertaken through a combination of 6-monthly patient questionnaires and linkage to routine healthcare databases

such as the UK Renal Registry, Hospital Statistics (for England/ Wales/ Scotland and/or Northern Ireland), Civil Registration (**Table 2**). Only data that are collected as part of routine care will be collected. Paper and electronic (web portal) options will be offered to patients for patient questionnaire completion.

Adherence to the protocol will be monitored through UK Renal Registry treatment modality returns and contact with dialysis units throughout the follow up. As the UK Renal Registry follows all patients on RRT in the UK, patients should not be lost to follow-up unless they move to another country.

### Table 2 Summary of follow-up data collection

Numbers in parentheses following diagnoses refer to the Healthcare Cost and Utilisation Project Clinical Classification System for mapping diagnoses onto ICD-10 [www.hcup-us.ahrq.gov](http://www.hcup-us.ahrq.gov).

|                                                       | Data items                                                                                                                                                                                                                                                                                                                                                                                                                                                                                                                                                                                                                                                                                                                                                                                                                                              | Source                               |
|-------------------------------------------------------|---------------------------------------------------------------------------------------------------------------------------------------------------------------------------------------------------------------------------------------------------------------------------------------------------------------------------------------------------------------------------------------------------------------------------------------------------------------------------------------------------------------------------------------------------------------------------------------------------------------------------------------------------------------------------------------------------------------------------------------------------------------------------------------------------------------------------------------------------------|--------------------------------------|
| Routine laboratory data                               | Creatinine, urea, Kt/V, urea reduction ratio, albumin, haemoglobin, haematocrit, mean corpuscular volume, sodium, potassium, bicarbonate, corrected calcium, phosphate, c-reactive protein, intact parathyroid hormone, total cholesterol.                                                                                                                                                                                                                                                                                                                                                                                                                                                                                                                                                                                                              | UKRR                                 |
| Cardiovascular and infections hospital admission data | 
Cardiovascular: Nonspecific chest pain (102), Congestive heart failure; non-hypertensive (108), Coronary atherosclerosis (101), Other circulatory disease (117), Acute myocardial infarction (100), Peripheral and visceral atherosclerosis (114), Chronic ulcer of skin (199), Gangrene (248), Aortic; peripheral; and visceral arterial disease (115), Transient cerebral ischemia (112), Cardiac arrest and ventricular fibrillation (107), Pulmonary heart disease (103), Other and ill-defined cerebrovascular disease (111), Acute cerebrovascular disease (109).
 
Infection: Pneumonia (122), Septicemia (except in labour) (2), Pleurisy; pneumothorax; pulmonary collapse (130), Aortic and peripheral arterial emboli (116), Tuberculosis (1), Mycoses (4), HIV infection (5), Encephalitis (77), Meningitis (76),
 | Hospital Statistics (HES, PEDW, ISD) |

|                                  |                                                                                                                                                                                                                                                                                                                                                                                   |                                                                  |
|----------------------------------|-----------------------------------------------------------------------------------------------------------------------------------------------------------------------------------------------------------------------------------------------------------------------------------------------------------------------------------------------------------------------------------|------------------------------------------------------------------|
|                                  | Shock (249), Skin and subcutaneous tissue infection (197), Fever of unknown origin (246), Infective arthritis and osteomyelitis (201), Bacterial infection; unspecified site (3), Other inflammatory condition of skin (198), Other infections; including parasitic (8), Influenza (123), Urinary tract infections (159), Genitourinary symptoms and ill-defined conditions (163) |                                                                  |
| Mortality data                   | Non-cancer mortality (i.e. all causes of death excluding chapter II causes in ICD-10).                                                                                                                                                                                                                                                                                            | NHS Spine tracing, UKRR, Hospital Statistics, Civil Registration |
| Patient reported outcomes        | EQ-5D-5L, DSI and Time to recovery (following dialysis) (5).                                                                                                                                                                                                                                                                                                                      | Patient questionnaire administered 6 monthly                     |
| RRT use                          | Frequency, machine, dialyzer, dialysis times and consumables used.                                                                                                                                                                                                                                                                                                                | Annual census (extracted from the renal IT system).       |
| Other hospital admissions | Day case and inpatient hospital admissions (including surgical procedures performed),                                                                                                                                                                                                                                                                                             | Hospital Statistics (HES, PEDW, ISD)                             |
| Patient reported healthcare use  | Nursing home/residential home days/hospice days, and primary care, community services and medication usage in the last 6 months.                                                                                                                                                                                                                                                  | Patient questionnaire administered 6 monthly                     |
| Blood stream infections          | Methicillin resistant staphylococcus aureus, Methicillin sensitive staphylococcus aureus, Clostridium difficile, and Escherichia coli, as report by mandate to PHE/ the UKHSA                                                                                                                                                                                                     | Reported to PHE/ UKHSA and shared with UKRR                      |

Numbers in parentheses following diagnoses refer to the Healthcare Cost and Utilisation Project Clinical Classification System for mapping diagnoses onto ICD-10 [www.hcup-us.ahrq.gov](http://www.hcup-us.ahrq.gov).  
Abbreviations: HES = Hospital Episode Statistics; ICD = International Classification of Diseases; ISD =

Information Services Division; PEDW = Patient Episode Database for Wales; PHE=Public Health England; UKHSA = UK Health Security Agency; UKRR = UK Renal Registry

Adherence to the protocol will be monitored through monthly reports from sites during recruitment reducing to three-monthly during follow-up. For the purposes of reporting only the last recorded dialysis session of each month will be examined. The log will include receipt of the allocated modality, attainment of high-volume HDF (if applicable), and water quality testing. Deviation from the protocol has been defined as (a) being off their allocated treatment on the last dialysis session of the month for two consecutive months and (for those allocated to high-volume HDF) (b) no longer aiming for high-volume HDF. This definition recognises that some patients need time to adjust their dialysis prescription and achieve their target substitution volume; indeed some, despite all best efforts, may never achieve it. It also recognises that patients may have short periods off their allocated treatment due to admission to hospital or travel with dialysis in another centre.

As the UKRR follows all patients on kidney replacement therapy in the UK, patients should not be lost to follow-up unless they move to another country or opt out of data linkage after being randomised.

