#### 3.4 Primary endpoint/outcome

A composite of first of non-cancer mortality or admission to hospital related to a cardiovascular event or infection (UKRR, Hospital Statistics & Civil Registration (CR)).

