#### **Plans to promote participant retention and complete follow-up**

As the primary outcome relies on data linkage with national routine healthcare databases, participants will only be lost to follow up if they opt out of data linkage after being randomised. Patients who discontinue allocated treatment can choose to continue to receive questionnaires and allow data linkage. The minimum number of identifiers will be used to link with routine data sources, as agreed with those organisations and set out in the participant information sheet. For patient-reported outcomes, up to three reminders are sent.

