## **9 STATISTICS AND DATA ANALYSIS**

### **9.1 Sample size calculation**

We anticipate that at 3 years of follow-up 65% of patients on HD will have experienced our composite endpoint and we plan to detect a HR of 0.75. This effect size was agreed to be clinically significant at an investigator meeting involving patients and health care professionals. We assume any effect will be attenuated by (i) cross-over between arms (15% HD to HDF & 5% HDF to HD) and (ii) participants being allowed to take part in other trials simultaneously. To optimise recruitment and avoid excluding eligible patients because they are already participating /want to participate in other trials, an additional adjustment has been made that assumes up to half of patients in both groups will take part in another trial that assigns half of these to an intervention that reduces our composite end-point (HR=0.9), the anticipated proportion experiencing an event on HD will be 62.5% (37.5% surviving event-free) & on HDF it will be 54.1% (45.9% surviving event-free) giving a revised HR of 0.79. The number of events required to detect this difference with 90% power and a 5% significance level is 801, which requires 1348 participants in total. The primary analysis will be intention to treat and to avoid informative censoring participants will not be censored for transplant (10). Allowing for 10% loss to follow-up for other reasons we require 1527 participants and will recruit 1550.

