#### **9.3.3 Secondary outcome analysis**

The secondary outcomes of all-cause mortality, non-cancer mortality, cardiovascular mortality, infection mortality will be analysed and reported in a similar manner to the primary outcome as described in section 9.3.2.

Cardiovascular and infection-related hospitalisations and MRSA and MSSA infections are all recurrent events and analyses of such outcomes should account for informative censoring due to death. We will therefore use joint frailty models (JFMs) as these simultaneously analyse recurrent events (infections or hospitalisations) and time to death while estimating distinct hazard ratios. Appropriate repeated measures regression models for patient-reported outcomes will be chosen based on the distribution of the data and will adjust for stratification variables and values of the outcome at the time of randomisation. A similar repeated measures regression approach will be taken to the following other repeated measure outcomes: time to recover after each dialysis session, haemoglobin levels, erythropoiesis stimulating agent dose, calcium levels, phosphate levels, PTH levels, albumin levels, and phosphate binder dose.

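### The cardiovascular code list counts heart failure only under a category titled non-hypertensive, so by its title hypertensive heart failure is left out of the primary composite and the cardiovascular hospitalisation outcome without a stated reason

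*Protocol*

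**What the plan says.** Section 3.4 defines the primary endpoint as "A composite of first of non-cancer mortality or admission to hospital related to a cardiovascular event or infection". The retention paragraph in section 7.6 explains how it is ascertained: "As the primary outcome relies on data linkage with national routine healthcare databases". The coded hospital record therefore decides whether an admission is an event.

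Table 2 lists the diagnoses that make up cardiovascular and infection admissions. The key to the numbers reads "Numbers in parentheses following diagnoses refer to the Healthcare Cost and Utilisation Project Clinical Classification System for mapping diagnoses onto ICD-10". The cardiovascular part has 14 categories. The only one for heart failure is "Congestive heart failure; non-hypertensive (108". The broadest residual entry is "Other circulatory disease (117", and the list ends with "Pulmonary heart disease (103), Other and ill-defined cerebrovascular disease (111), Acute cerebrovascular disease (109". A separate row of the table covers all other hospital admissions.

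Section 9.3.3 analyses the same admissions again as a secondary outcome: "Cardiovascular and infection-related hospitalisations and MRSA and MSSA infections are all recurrent events". These go into joint frailty models alongside death.

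**The concern.** Because category 108 is on the list, heart failure was meant to be among the cardiovascular events. The limit to the non-hypertensive form comes with the classification's category title, and the protocol neither explains it nor adds a category for the hypertensive form. If the title describes the content, two patients admitted with the same illness could be classified differently according to whether the coder linked the heart failure to hypertension.

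Two outcomes are affected. In the primary composite, a missed heart-failure admission is either postponed to the next qualifying event or lost. In the recurrent cardiovascular hospitalisation outcome, a missed admission is simply not counted: cardiovascular death is analysed separately and does not stand in for it.

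**Working it through.** **1. The list.** The cardiovascular categories in Table 2, in numerical order, are 100, 101, 102, 103, 107, 108, 109, 111, 112, 114, 115, 117, 199 and 248, which makes 14. One (108) is heart failure and is labelled non-hypertensive. None names hypertension or hypertensive heart disease. The 19 infection categories do not either. No section adds such a category, explains its absence or provides for clinical adjudication that could override the coding.

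**2. The list applied by its titles.**

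| Admission as coded | Counts through that code? |
|---|---|
| Heart failure, no hypertensive code | Yes (108) |
| Heart failure due to hypertension | Not by the title of 108; only if the map places it in a listed category, or another listed code is present |
| Nonspecific chest pain | Yes (102) |

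**3. The plan's event count.** Inputs from section 9.1: 37.5% event-free on HD and 45.9% on HDF, 90% power, 5% significance (taken as two-sided), 1:1 allocation, 801 events. The proportions come from: "the anticipated proportion experiencing an event on HD will be 62.5% (37.5% surviving event-free) & on HDF it will be 54.1"%.

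- HR = ln(0.459)/ln(0.375) = 0.794.
- Freedman events = [(1.96 + 1.2816) × (1 + HR)/(1 − HR)]² = (3.2416/0.11487)² ≈ 797.
- Schoenfeld's formula gives 790.

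Both are within 2% of 801, so the planned figure is reproduced closely enough to use as the baseline.

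**4. Size under assumptions.** The protocol gives neither the heart-failure share of first events nor the share of those coded as hypertensive. Assume 5–15% for the first and 10–50% for the second.

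- Low: 5% × 10% = 0.5%; 0.005 × 801 ≈ 4 events.
- Middle: 10% × 30% = 3%; 0.03 × 801 ≈ 24 events.
- High: 15% × 50% = 7.5%; 0.075 × 801 ≈ 60 events.

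If half of these patients have a later qualifying event, the range halves to 2–30.

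Power = Φ(√events × (1 − HR)/(1 + HR) − 1.96), with HR = 0.794 and no replacement:

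| Events | Power |
|---|---|
| 801 | 90.2% |
| 797 (low) | 90.0% |
| 777 (middle) | 89.3% |
| 741 (high) | 87.8% |

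The largest drop is about 2.3 points (2.4 if HR is rounded to 0.795). With half replaced in the high case (771 events), power is 89.1%.

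**5. The cardiovascular hospitalisation outcome.** On the same assumption, 10–50% of heart-failure admissions would go uncounted, less any that carry another listed code.

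**The case against.** The strongest objection is that a category title is not the classification map. The map from ICD-10 codes to these categories is outside the protocol, so the document does not show where a code for hypertensive heart failure goes; category 117 is on the list and might take some. This stands, and it makes the map check the first step. It does not remove the point: the one heart-failure category carries a title that excludes the hypertensive form, and nothing in the protocol says that form is picked up elsewhere.

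A second objection is that Table 2 is a summary of data collection and that exact codes belong in a statistical analysis plan. A plan not shown here may well extend the list. But the protocol does not leave the list open: it prints numbered categories and puts all other admissions in a separate row. A later plan would either inherit the gap or depart from the protocol.

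A reader might also infer more than the documents support:

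- *That identical admissions are certain to be classified differently.* The protocol does not say which diagnosis position counts, so another listed code on the same record could make the admission an event.
- *That the treatment comparison is biased.* Nothing shows coding that differs by arm. Randomisation is stratified by site and the analysis adjusts for the stratification variables, so hospital coding habits should be balanced between arms.
- *That coding of hypertension varies by site or nation.* Several national databases are used, but the protocol gives no evidence on how coding differs among them.
- *That the trial is underpowered.* The frequencies are assumed and the effect is small. The 801 events rest on 3-year proportions, whereas follow-up runs from 32 to 91 months and the recruitment target of 1550 exceeds the 1527 required. The anticipated 65% event proportion on HD may already reflect this code list, in which case no planned events are lost.

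**Conclusion.** The point holds as one of endpoint definition. The only operational list of cardiovascular admissions includes heart failure solely under a category whose title excludes the hypertensive form, with no reason given. Whether a heart-failure admission counts may therefore depend on how hypertension was coded. This weakens the validity and consistency of the primary composite and, more directly, of the recurrent cardiovascular hospitalisation outcome.

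The conclusion rests on reading category 108 by its title, subject to the map. How often it matters cannot be established from the document, and the cost in power is probably small. It should be corrected, but it does not threaten the trial's main comparison.

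**What to change.** First check the classification map to see where codes for heart failure with hypertension fall. If they already fall in a listed category, say so in Table 2. If not, add to the cardiovascular list the specific codes for hypertensive disease with heart failure. Adding a whole hypertension category is not advisable, since it could bring in admissions without heart failure. If the exclusion was intended, give the reason instead.

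Make the change blind to arm and before any comparison by arm. Use the revised list for both the primary composite and the cardiovascular hospitalisation outcome, and report the list as now printed as a sensitivity analysis.

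The cost is one line in Table 2 and in the code list. All hospital admissions are already obtained by linkage, so no new data are needed. The small downside is a documented change to the endpoint code list.

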#### **Plans to promote participant retention and complete follow-up**

As the primary outcome relies on data linkage with national routine healthcare databases, participants will only be lost to follow up if they opt out of data linkage after being randomised. Patients who discontinue allocated treatment can choose to continue to receive questionnaires and allow data linkage. The minimum number of identifiers will be used to link with routine data sources, as agreed with those organisations and set out in the participant information sheet. For patient-reported outcomes, up to three reminders are sent.

